## **Secondary Objectives**

1. The likelihood of disease detected on PSMA PET will be correlated with absolute PSA level at the time of PSMA PET as supplied on the eligibility form.
2. The proportion of men with oligometastatic recurrence (four or fewer sites including the prostate bed if positive) detected on PSMA PET will be calculated as the number of men with 4 or fewer lesions identified as +5 (definitely malignant) or +4 (probably malignant) divided by the number of men with any number of +5 or +4 lesions detected.
3. The number of men who have a change in management will be determined by comparison of the management questionnaire obtained at the time of registration to the repeat questionnaire performed after the PSMA PET scans are reported.
4. Actual management within 6 months will be determined through linkage to existing health information registries and will include:
  - a. Delivery of radiotherapy (anatomic site, dose and fractionation) – Cancer Care Ontario
  - b. Biopsy of suspected recurrences (anatomic site, histology) – Provincial pathology database
  - c. Use of salvage lymph node dissections – CIHI
  - d. Use of salvage hormonal therapy/androgen deprivation
5. PSA response will be examined by comparing 6 month PSA against PSA at the time of PSMA PET through the Ontario Laboratory Information Services and correlated with actual management as determined in 4.
6. Comparison of the detection rates of PSMA PET/CT when conventional imaging is used as part of eligibility criteria (PREP) versus when conventional imaging is omitted (PREP Phase 2)

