## **Secondary Objectives**

1. Determine correlations between PSA levels at time of imaging and presence of disease detected on PSMA PET
2. Determine the proportion of men with oligometastatic recurrence (four or fewer sites including the prostate bed if positive) detected on PSMA PET as calculated by the number of men with 4 or fewer lesions identified as +5 (definitely malignant) or +4 (probably malignant) divided by the number of men with any number of +5 or +4 lesions detected.
3. Determine the number of men who have a change in management as indicated by responses from referring physicians on an impact questionnaire completed after PSMA PET scans are reported.
4. Determine the actual management delivered within 6 months by linkage to existing health information registries:
  - a. Delivery of radiotherapy (anatomic site, dose and fractionation) – Cancer Care Ontario
  - b. Biopsy of suspected recurrences (anatomic site, histology) – Provincial pathology database
  - c. Use of salvage lymph node dissections – CIHI
  - d. Use of salvage hormonal therapy/androgen deprivation
5. Compare PSA response at 6 months against PSA at the time of PSMA PET obtained through linkage to the Ontario Laboratory Information Services and correlate with actual management as determined in 4.
6. To compare the detection rates of PSMA PET/CT when conventional imaging is used as part of eligibility criteria (PREP) versus when conventional imaging is omitted (PREP Phase 2)

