### **Inclusion Criteria**

1. Written informed consent obtained
2. Male, Age  $\geq$  18 years
3. Prior primary treatment for prostate cancer with curative intent such as radical prostatectomy **or** radiotherapy for localized prostate cancer. Unless PET/CT requested as part of Cohort 7.
4. Suspected persistent or recurrent disease defined as one of the following:
  - a. High risk disease at the time of radical prostatectomy characterized by pathologically involved node(s) **or** persistently detectable PSA (>0.1ng/ml) within 3 months post-surgery
  - b. Primary treatment for prostate cancer and biochemical failure (BF) with current management according to the following:
    - i. Following primary radical prostatectomy, BF is defined as rising PSA on at least 2 occasions measured at least 1 month apart and with the most recent PSA measured at >0.1 ng/ml
    - ii. Following primary radiotherapy for localized disease, BF is defined according to the Phoenix Definition, which is rising PSA on at least 2 occasions measured at least 1 month apart and with the most recent PSA measured greater than the nadir PSA + 2.0 ng/ml.

Unless PET/CT requested as part of Cohort 7.
5. Patient scenario falls into one of the 7 pre-defined cohorts. When patient scenario falls outside cohorts 1-6 participation in the Registry must be approved through the established CCO adjudication process for cohort 7.
6. Conventional imaging consisting of bone scan and abdo-pelvic CT scan within 3 months of registration that is either equivocal, negative (no lesions) or positive for oligometastatic disease (4 or fewer unequivocal lesions identified). Registration is defined as Form A: Eligibility is complete.
7. Karnofsky performance status 70 or better (ECOG 0, 1)

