### ***Patient Approval for PSMA PET/CT***

Registration materials for the requested PSMA PET as part of the registry will be sent to the local PET Centre participating in the registry and reviewed by the local Imaging investigator. Provided all eligibility criteria are met and pre-imaging questionnaires are completed the PSMA PET scan will be scheduled within 6 months of registration. Cancer Care Ontario will also receive registration materials for the purposes of tracking patients on the registry and reimbursement for the PSMA PET/CT scans.

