#### *Sample Size Revision, Cohorts 2, 3, 6*

A recent meta-analysis by Perera et al (27) of 37 studies and 4790 patients focused on the performance of 68Ga-PSMA in primary staging as well as restaging of men with biochemical failure after radical prostatectomy or radiotherapy. They found a detection rate of 0.48 (PSA 0.2-0.49) to 0.97 (PSA>2) depending on the PSA at time of imaging following biochemical failure. In order to demonstrate that 18F-DCFPyL provides a similar detection rate as described by Perera et al for 68Ga-PSMA based agents, we will increase our sample size for cohorts 2, 3 and 6. To allow us to estimate the detection rate with a precision of +/-5% (with 95% confidence), assuming a detection rate of 60%, we will require 369 patients per cohort, 425 assuming a 15% dropout rate. With cohorts 1, 4, 5 and 7 remaining at 65 men each according to the original endpoint, this will result in a total sample size of 1535 men.

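### Secondary outcome 1 labels as scan-time PSA a value taken from the eligibility form, which may be completed up to 6 months before the scan

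*Protocol*

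**What the plan says.** Secondary objective 1 of the Protocol (Objectives) is to "Determine correlations between PSA levels at time of imaging and presence of disease detected on PSMA PET". The matching item 1 under Outcomes Assessment says how: detection will be "correlated with absolute PSA level at the time of PSMA PET as supplied on the eligibility form".

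Other sections fix the timing:

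- Inclusion Criteria, in both the PREP and the Phase 2 lists: "Registration is defined as Form A: Eligibility is complete". The form is therefore finished at registration.
- Patient Approval for PSMA PET/CT: "the PSMA PET scan will be scheduled within 6 months of registration".
- Inclusion Criteria, item 4b, after prostatectomy: "BF is defined as rising PSA on at least 2 occasions measured at least 1 month apart". The criterion after radiotherapy also requires a rise. Neither limits the age of the most recent PSA. Where conventional imaging is required, it does have a limit: 3 months before registration.

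Item 5 under Outcomes Assessment uses the same label for a PSA: "PSA response will be examined by comparing 6 month PSA against PSA at the time of PSMA PET through the Ontario Laboratory Information Services".

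**The concern.** The label and the stated source do not agree. A form completed before the scan is booked cannot be relied on to give the PSA on the day of the scan. This is not a detail left open for an analysis plan. The Protocol names the source, and an analyst who follows it will report a registration PSA as a scan-time PSA.

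In men who enter with a rising PSA the error has a likely direction. PSA tends to go on rising between the form and the scan, so a lesion found at the higher value is credited to the lower one. Detection at low PSA then looks better than it is. Low PSA is where readers will look, because the Protocol itself describes detection as steeply dependent on PSA. Of the cited meta-analysis, the sample size revision for Cohorts 2, 3 and 6 says: "They found a detection rate of 0.48 (PSA 0.2-0.49) to 0.97 (PSA>2) depending on the PSA at time of imaging". Any PSA-specific reading of the registry against such rates needs PSA on the same time basis.

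**Working it through.** The Protocol gives no figure to reproduce here. The check compares the sections and then sets a scale under stated assumptions.

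**1. Timeline from the document.** The order is PSA drawn (age not limited), form completed (which is registration), then scan (0 to 6 months later). The lag L from blood draw to scan is therefore the wait after registration plus the unstated age of the PSA at registration. L can exceed 6 months.

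**2. Drift of PSA over the lag.** Assume exponential growth with doubling time D. The Protocol gives no doubling times, so D is an assumption.

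PSA at scan = form PSA × 2^(L/D)

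| Assumed D (months) | L = 3 months | L = 6 months |
|---|---|---|
| 3 | 2.0 | 4.0 |
| 6 | 1.41 | 2.0 |
| 12 | 1.19 | 1.41 |
| 24 | 1.09 | 1.19 |

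A form PSA of 0.3 ng/ml would be 0.3 × 1.19 = 0.36 to 0.3 × 4 = 1.2 at a scan 6 months later. A form PSA of 0.4 with D = 6 months becomes 0.4 × 2 = 0.8. That crosses the 0.5 ng/ml boundary used in the 38-man comparison in the Background, where PSMA detection was 50% below 0.5 and 69% from 0.5 to 2.0.

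**3. Effect on the association and on detection at a given PSA.** This is an illustrative simulation of 400,000 men with all inputs assumed:

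- form PSA lognormal, median 1.0 ng/ml, log-SD 1.2;
- doubling time lognormal, median 9 months, log-SD 0.7;
- logit(detection) = 0.4 + 0.9 × ln(PSA at scan);
- wait and doubling time independent of form PSA;
- every man's PSA rising.

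Bands are cut at 0.2, 0.5, 1 and 2 ng/ml.

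| Wait to scan | Men in a different band | Detection at 0.2–0.5: by form / by scan PSA | Detection at 0.5–1: by form / by scan PSA | Log-PSA slope: form / scan |
|---|---|---|---|---|
| none | 0% | 36% / 36% | 53% / 53% | 0.903 / 0.903 |
| uniform 0–3 months | 15% | 39% / 36% | 56% / 52% | 0.894 / 0.898 |
| uniform 0–6 months | 26% | 42% / 36% | 59% / 52% | 0.885 / 0.898 |
| all 6 months | 46% | 48% / 36% | 65% / 52% | 0.875 / 0.898 |

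The pattern has a simple cause. At the median doubling time, a 6-month lag adds ln 2 × 6/9 = 0.46 to log PSA, and so 0.9 × 0.46 = 0.42 to the logit, whatever the form PSA. The curve shifts upward at each form PSA and its slope barely changes.

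**4. Item 5.** The phrase about the laboratory service can be read in two ways. If it covers both PSA values, items 1 and 5 take a PSA with the same label from different sources. If it covers only the 6-month value, the scan-time PSA in item 5 has no stated source.

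**The case against.** The other side has a good deal to say, and most of it limits the size rather than the existence of the problem.

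- Six months is a ceiling. The document gives no distribution of waits and no doubling times, so the larger factors need the full wait and fast growth. This stands.
- A reader might infer that the whole PSA–detection relationship is distorted. The documents do not support that. Item 1 plans a correlation, no PSA-banded rates are specified, and the slope hardly moves in the illustration above. What shifts is the level of detection at a given low PSA.
- A reader might infer that the comparison with the cited meta-analysis fails. That section plans ±5% precision around an overall rate of 60% per cohort and defines no PSA-banded comparison. The harm arises only if results are read by PSA.
- The form value does not understate scan PSA in every man. Cohort 1 can enter on positive nodes alone, Cohort 7 is exempt from the biochemical failure criterion, and a treatment change before the scan could lower PSA.
- Item 5 is too loosely worded to be called a correct definition already in place. It states no window and no rule about intervening therapy.
- The 50% and 69% bands come from one small study of a different tracer. They show that a boundary can be crossed, not how large the error would be in this registry.

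None of this removes the conflict between label and source.

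**Conclusion.** The inconsistency is in the text and should be corrected. Item 1 calls a registration PSA a scan-time PSA, with up to 6 months between registration and scan and no limit on the age of the blood test. In men who qualify by a rising PSA, detection at a given low PSA would tend to be overstated.

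The size is not known. With a 6-month lag the factor is 4, 2 or 1.4 at assumed doubling times of 3, 6 or 12 months. If waits are spread evenly over 0 to 6 months, the illustration gives 42% against 36% at 0.2–0.5 ng/ml. These figures rest on assumed growth, waits and detection curve.

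The primary endpoint does not use PSA and is unaffected. The finding concerns one secondary outcome, which the Statistical Analyses section treats descriptively, and the wording of a second.

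**What to change.** In Outcomes Assessment, item 1, define scan-time PSA as the linked Ontario laboratory value nearest to and before the scan, within a stated window (30 days would be one choice) and before any new therapy. Use the same definition in item 5 and say plainly which source supplies each of its two PSA values.

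Keep the form value only as a fallback, labelled as PSA at registration. Record the date of each PSA and the interval from PSA to scan, and add a sensitivity analysis limited to men with short intervals.

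The cost is a change of wording and some added date fields. Linkage to the provincial laboratory data is already planned, so no extra visit or blood test is needed. The drawback is that no PSA is required at the scan, so some men will have no value nearer to it than the one on the form. For them the lag remains, but it will be visible.

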## **ADVERSE EVENTS**

This study will be conducted in accordance with Health Canada regulatory requirements and ICH Good Clinical Practice guidelines. Only adverse events (AEs) and Serious Adverse Events (SAEs) data attributable to the investigational imaging [18F]DCFPyL PET/CT will be tracked and reported.

### *Adverse Event Definitions*

An Adverse Event (AE) is defined as any untoward medical occurrence in a patient who is administered a drug or biologic (medicinal product) or using a medical device; the event does not necessarily have a causal relationship with this treatment or usage. An AE can therefore be any unfavourable and unintended sign (including an abnormal laboratory finding), symptom, or disease temporally associated with the use of a medicinal (investigational) product, whether or not related to the medicinal (investigational) product. Each AE is to be classified by the Investigator as serious or non-serious.

A Serious Adverse Event (SAE) is any untoward medical occurrence that at any dose:

1. results in death
2. is life-threatening (i.e., immediate risk of death),
3. requires inpatient hospitalization or prolongation of existing hospitalization, except pre-planned hospitalizations required as part of a standard procedure or cancer treatment,
4. results in persistent or significant disability / incapacity,
5. is a congenital anomaly / birth defect

OR

6. is an important medical event, which is not immediately life threatening or requiring hospitalization, but may otherwise jeopardize the patient or may require intervention to prevent other outcomes specified in the above definition of SAE

An AE is unexpected when the nature or severity of the AE is not consistent with the applicable product information (i.e., Investigators Brochure for an unapproved investigational product or package insert/summary of product characteristics for an approved product). An AE is considered to be associated with the use of the drug if the attribution is classified as “Possible”, “Probable” or “Very Likely”.

#### Attribution Definitions

1. Unrelated: An AE which is not related to the use of the study drug.
2. Unlikely: An AE for which an alternative explanation is more likely (e.g. concomitant medication, concomitant disease), and/or the relation with time suggests that a causal relationship is unlikely.
3. Possible: An AE which might be due to the use of the study drug. An alternative explanation (e.g., concomitant medication, concomitant disease) is inconclusive. The relationship in time is reasonable; therefore the causal relationship cannot be excluded.
4. Probable: An AE which might be due to the use of the study drug. The relationship in time is suggestive (e.g., confirmed by a de-challenge). An alternative explanation is less likely (e.g., concomitant medication, concomitant disease).
5. Definitely Related: An AE, which is listed as a possible adverse reaction and cannot be reasonably explained by an alternative explanation (e.g., concomitant medications, concomitant diseases). The relationship in time is very suggestive (e.g. it is confirmed by a de-challenge and a re-challenge).

#### *Adverse Event Reporting Criteria*

AEs and SAEs will be considered related to study if they are related specifically to the [18F]DCFPyL PET/CT imaging. Progression of cancer and complications related to conventional imaging or cancer treatment (e.g. surgery, chemotherapy and/or radiotherapy) are expected and bear no relationship to the imaging protocol, therefore they will not be documented as AEs or SAEs for the purpose of this Registry. Deaths due to recurrent cancer are also expected and will not be reported as SAEs for the purpose of this Registry. Whenever possible, symptoms should be grouped as a single syndrome or diagnosis. The Investigator should specify the date of onset, grade, action taken with respect to the imaging protocol, corrective treatment or therapy given, outcome and his/her opinion as to whether there is a reasonable possibility that the AE was related to the imaging protocol. The severity of all AEs will be graded according to the NCI CTCAE, version 4. For each event, the highest severity grade attained since the last assessment period will be reported. If a CTCAE score does not exist, the Investigator should assess the event as Grade 1 (mild), Grade 2 (moderate), Grade 3 (severe), Grade 4 (life-threatening or disabling) or Grade 5 (causing death) to describe the maximum intensity of the AE.

#### *Adverse Event Reporting Period*

The AE reporting period for this study begins at the time of imaging and continues until 30 days after the imaging is completed. In the case of an SAE, the patient will be followed until clinical recovery or until progression has been stabilized or judged to be chronic.

#### *Serious Adverse Event Reporting*

Adverse events considered to be SERIOUS and UNEXPECTED and RELATED (that is, attributed as Possibly, Probably, or Very Likely) to the [18F]DCFPyL PET/CT imaging, must be recorded on a Serious Adverse Event Form and be reported by the site Investigator to the Sponsor, the REB, and regulatory authorities within the required timelines.

- Sponsor: within 24 hours of becoming aware of the event.
- OCREB: within 48 hours from the time the Investigator becomes aware of the event.
- Health Canada: within 7 days if SAE is fatal or life threatening, and 15 days if NOT fatal or life threatening.

All other SAEs should be reported within 5 days from the time when the site personnel became aware of the event.

Follow-up reports must be submitted to the Sponsor, the REB, and regulatory authorities when new information becomes available and not later than 5 days after the clinical site personnel became aware of the event. If an ongoing SAE changes in its intensity (Grade) or relationship to the Investigational Product, a follow-up SAE report should be sent immediately.

In the rare event that the Investigator does not become aware of the occurrence of an SAE immediately, the Investigator is to report the event to the REB, the Sponsor and regulatory authorities within 24 hours of notification of the event.

## **STUDY ADMINISTRATION**

### **Ethical and Regulatory Standards**

#### *Informed Consent*

It is the responsibility of the local Investigator or a person designated by the local Investigator and under the Investigator's responsibility, to provide each potential study patient, prior to inclusion in the study, full and adequate verbal and written information regarding the objectives and procedures of the study and the possible risks involved. The patient must be informed about their right to withdraw from the study at any time. The patient must be allowed adequate time to make an informed decision. Prior to a patient's participation in the study, the locally approved Information and Consent Form (ICF) must be signed, name filled in and personally dated by the patient or by the patient's legally acceptable representative, and by the person who conducted the informed consent discussion. A copy of the signed and dated written consent form document and any other written information will be provided to the patient. Written informed consent will be obtained from all potentially eligible patients prior to commencing any study procedures. Until the patient has been completely informed of the clinical trial, has freely consented to take part in the study and has signed and dated an informed consent form that has received documented approval by a licensed Research Ethics Board, no study related procedures can be performed.

#### *Research Ethics Board (REB)*

This Registry will utilize the Ontario Cancer Research Ethics Board (OCREB) as the Board of Record. Prior to the commencement of the Registry, the Investigator must submit this clinical trial protocol, the ICF document, Investigator Brochure or product labeling information, recruitment materials/process, patient questionnaires, and any other written information to be provided to study patients to the appropriate Ethics Committee (OCREB) and is required to forward to the sponsor a copy of the written and dated approval/favourable opinion signed by the Chairman with Ethics Committee (OCREB) composition. The clinical trial (study number, clinical trial protocol title, version number and version date), the documents reviewed (clinical trial protocol, Informed Consent Form, Investigator's Brochure, etc.) and the date of review should be clearly stated on the written (OCREB) approval/favourable opinion. Any amendments or modification to the study protocol and/or Informed Consent Form document must be submitted to and approved by the Ethics Committee (OCREB). The Ethics Committee (OCREB) should also be informed of any event likely to affect the safety of patients or the continued conduct of the study. Annual re-approval is required for as long as the study is open to patient accrual and/or patients are being followed and evaluated. The Ethics Committee (OCREB) must be informed when the study is closed or has been suspended.

#### *Confidentiality of Registry Participant Records*

The names and personal information of study participants will be held in strict confidence. Personal identifying information (name, date of birth, postal code, telephone number and OHIP number) will be sent to the local PET Centres participating in the registry to review participant eligibility and to CCO to track registry participants. This information, together with other information collected for the registry, will be kept confidential and securely transferred to Cancer Care Ontario and linked with routinely-collected information about the study participant's health care found in existing health-related databases (e.g., the Provincial Pathology Database, Canadian Institute for Health Information (CIHI), and the Ontario Laboratory Information Services).

The primary investigator at each participating site will maintain a confidential subject identification list (Master List) during the course of the study. Access to confidential information (i.e., source documents and patient records) is only permitted for direct subject management and for those involved in monitoring the conduct of the study (i.e., Sponsors, representatives of the REB, and regulatory agencies). The participant's name will not be used in any public report of the study.

All imaging data ([18F]DCFPyL PET/CT scans) and reports will be stored in the participating sites' hospital medical records and will be accessible to physicians within the participant's circle of care.

